### Randomization and Allocation Concealment

Random numbers will be generated by a computerized random number table generator through the stratified block randomization method of the SAS package (Version 9.4; SAS institute Inc., Cary, NC, USA) with a random block size. The random number table will be prepared by an independent, blinded statistician. Two block numbers will be randomly used to prevent allocation guessing by researchers. A stratified random number table will be generated according to the severity of chronic neck pain (PI-NRS score range from the 4 to 6 group vs the 7 to 10 group). The random number table file will be protected by a password, and the independent, blinded statistician, who is not involved in the recruitment, acupuncture treatment or assessment, will manage the table. A random allocation will be conducted at visit 1 to participants who provide informed consent. When a participant meets the inclusion criteria, the two types of treatment will be explained to him or her. Acupuncture will be explained as “classical acupuncture, typically used in Korean medicine clinics” and sham acupuncture as “non-classical acupuncture, rarely used in Korean medicine clinics” [14]. To ensure allocation concealment, the participants will be randomized according to the random number table by the independent researcher, and the allocated group information will be sent by an e-mail. The e-mail will be printed out and stored as a source document.

### Blinding

The participants, outcome assessor, data managers and statistician will be blinded to the allocation. The participants will be treated in the similar environments of a Korean Medicine clinic or hospital setting. All the participants will be treated with PSD regardless of the group so the participants cannot guess the allocated group by the appearance of the acupuncture. The blind will be maintained until locking of the data. To evaluate blinding, allocation guessing and a credibility rating will be assessed immediately after the first and last treatments. The practitioners and assessor are trained to treat participants according to pre-defined SOPs during the trial to maintain blindness.

### Intervention

The acupuncture treatment will be conducted by doctors of Korean medicine (DKMs) with more than 6 years of Korean medicine college education and at least 8 years of clinical experience.

To ensure the same conditions except for the needling components [15] between the groups, all the treatment procedures and regimens will be described in detail in pre-specified protocols and SOPs. A moderate interaction between the practitioners and participants is allowed: at each visit before the treatment, the practitioner will ask the participant about recent symptoms and improvements and record the answers in the patient chart; the practitioner will touch the subject’s neck to determine the pain sites according to meridian sinews; the participant will be allowed to inquire about the treatment without restriction, but the practitioner will not be allowed to give confident or positive encouragement in response to questions concerning a prognosis. This information will be given to the practitioners in workshops conducted before the study begins to ensure a standardization of the treatments. The MMRM and sham acupuncture groups will receive a total of 8 sessions (2 sessions per week) of acupuncture treatment for 4 weeks. Each acupuncture treatment will be performed after the acupuncture points are sterilized with a disposable 70 % isopropyl alcohol swab. During the treatment, the participant will lie in a prone position with a cushion under the chest to ensure a stable position.

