**Discussion:**

The results of this trial will provide evidence to confirm the efficacy and safety of acupuncture for chronic neck pain.

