#### Myofascial-meridian release acupuncture (MMRA) treatment

The MMRA treatment is acupuncture protocol used at the Spine and Joint Clinical Center in Kyung Hee University Korean Medicine Hospital for patients with chronic neck pain. Chronic neck pain is related to local factors such as mechanical stress from the head or spine and systemic factors such as mental stress from psychosocial issues [16, 17]. Thus, the MMRA treatment was developed to reduce not only local factors by decreasing tissue adhesion [18] and myofascial trigger points [19, 20] but also systemic factors by promoting the flow of qi and blood [21] and reducing psychological factors [22].

A total of 8 acupuncture sessions will be performed using 0.25 × 40 mm disposable sterile acupuncture needles (Dongbang Acupuncture Inc., Chungnam, Republic of Korea). As for local points, a simple insertion technique is performed at EX-B2 and 5–10 tender points on the posterior neck followed by approximately 30 s of stretching, including flexion, extension, lateral bending and rotation. The acupuncture treatment is then performed at bilateral BL10, SI15, GB20, TE15 and CV14 using PSD and real needles. The needles are retained for 20 min, and the deqi sensation is induced by rotating the needles 3–5 times in a single direction (right and left if the patient expresses pain). A maximum of 4 individual acupuncture points are allowed. For distal points, a meridian diagnosis is carried out before the acupuncture treatment. If more than 2 meridians are diagnosed, a combination of acupuncture points from both meridians can be used.Greater yang meridian sinews (Smaller Intestine & Bladder meridian): BL65, SI3, Jeong-geun, Jeong-jongLesser yang meridian sinews (Triple Energizer & Gallbladder meridian): GB41, TE3, GB34, GB39Yang brightness meridian sinews (Large Intestine & Stomach meridian): LI11, Young-gol, Sang-bek, CV24.

After the meridian diagnosis is complete, 6 acupuncture points in the corresponding meridian group, as well as unilateral PC6 and HT7, will be chosen for the treatment. After penetration, the needles are retained for 20 min, and the deqi sensation is induced by rotating the needles 3–5 times in a single direction (right and left if the patient expresses pain). If CV24 is chosen, the needle should be rotated right and left for 30 s after penetration, during which time flexion stretching is performed, and then removed.

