#### Sham acupuncture treatment

Park sham device (PSD) will be used as sham acupuncture. It is a validated sham acupuncture device that is comprised of two tubes and a needle (either real or sham) [23]. The guide tube supports the needle when penetrating the skin vertically. A larger tube named ‘Park tube’ is attached on the ring base and lets the guide tube move along the ‘Park tube’. A silicon base is attached to the skin by a double-sided tape [13]. A placebo acupuncture needle of PSD is indistinguishable with real acupuncture, but cannot penetrate the skin. For local points, predetermined points on the posterior neck (0.5 cm from C4, 5, 6, 7 on both sides) are stimulated lightly 2 times using sham acupuncture with a blunt tip of the needle. Then, a sham acupuncture treatment is performed using the PSD and sham acupuncture needles on the points 0.5 cm away from C5 and 6 on both sides and right above the spine of scapula. The needles are retained for 20 min. For distal points, 1 cm to the inner side of both TE6 and 0.3 cm to the outer side of the highest point of both calcaneus are treated using the PSD and sham acupuncture needles. The needles are retained for 20 min without a de-qi sensation, creating a false movement that is similar to twisting acupuncture.

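### Only the MMRA arm is described as receiving neck stretching, against the stated principle that the arms differ in needling alone, so the comparison supports the MMRA package versus sham and not needling or acupuncture in general

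*Protocol article*

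**What the plan says.** All references are to the protocol article.

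- **Intervention** gives the reason for detailed procedures in both groups: "To ensure the same conditions except for the needling components [15] between the groups". It also describes, without limiting it to one arm, that at each visit "the practitioner will touch the subject’s neck to determine the pain sites according to meridian sinews".
- **Myofascial-meridian release acupuncture (MMRA) treatment** describes insertion at EX-B2 and tender points, "followed by approximately 30 s of stretching, including flexion, extension, lateral bending and rotation". If CV24 is chosen, the needle is rotated for 30 s, "during which time flexion stretching is performed, and then removed". On point selection: "For distal points, a meridian diagnosis is carried out before the acupuncture treatment".
- **Sham acupuncture treatment** sets out fixed local points that "are stimulated lightly 2 times using sham acupuncture with a blunt tip of the needle", then retained sham needles with the Park device at local and distal sites, with simulated twisting. It mentions no stretching.
- **Blinding** states: "All the participants will be treated with PSD regardless of the group".
- **Objective** is to assess MMRA (printed there as MMRM) against sham.
- **Abstract, Discussion** goes further and says the results will "provide evidence to confirm the efficacy and safety of acupuncture for chronic neck pain".

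**The concern.** A sham-controlled trial can attribute a difference to the needle only if everything else is held equal. The protocol claims that property and then describes a non-needling component in one arm only. The protocol itself regards neck movement as active: the Co-interventions section offers head and neck exercises and calls them effective for relieving neck pain. Cervical range of motion is a secondary outcome, measured in flexion, extension, lateral bending and rotation (Disability section), which are the directions stretched in the MMRA arm.

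What is at stake is the wording of the conclusion. If the trial is positive, a reader who relies on the control principle will credit needling, and one who relies on the Abstract will credit acupuncture in general. The described comparison cannot deliver either.

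**Working it through.** **1. The arms side by side**

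| Component | MMRA section | Sham section | Covered by the needling-only principle? |
|---|---|---|---|
| First local step | Insertion at EX-B2 and 5–10 tender points; Park device not named | Light blunt stimulation at fixed points; Park device not named | Yes, a needling difference; device described alike |
| Stretching after the first step | About 30 s, four directions | None described | No |
| Retained local needles | Park device, real needles | Park device, sham needles | Yes |
| Distal needles | Park device not named | Park device named | Unclear; may be condensed wording |
| Stretching with CV24 | Flexion, if CV24 is chosen | None described | No |
| Meridian assessment | Diagnosis selects the distal points | Fixed points, but palpation by meridian sinews is described for both groups in the Intervention section | Partly matched |

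Stretching is the firm contradiction. The other differences are needling differences, partly matched, or a matter of silence.

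**2. Why analysis cannot repair it**

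The difference between arms estimates needling effect + stretching effect + any joint effect. There is one contrast and at least two unknowns. No arm has stretching without needling, or needling without stretching. Variation in CV24 use does not help, because it follows the meridian diagnosis and is not randomised.

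**3. Amount of stretching**

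If given at each of the 8 planned sessions: 8 × 30 s = 240 s, about 4 minutes, apart from the CV24 stretch.

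**4. The plan's own sample size, reproduced**

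Inputs from the Sample size calculation section: difference 1.5, SDs of change 1.88 and 2.21, two-sided α 0.05, power 80%, drop-out 15%.

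- Pooled SD = √((1.88² + 2.21²)/2) = √((3.5344 + 4.8841)/2) = 2.052
- d = 1.5/2.052 = 0.731
- The noncentral t calculation gives 31 per group (power 80.8%); 30 per group gives 79.5%.
- 31/0.85 = 36.5, rounded up to 37 per group, 74 in total.

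The plan's 31 and 74 are confirmed and are not in dispute.

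**5. Illustration only**

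The documents give no stretching effect. Assume needling adds nothing and stretching is worth s points. With 31 per group, the noncentrality is (s/2.052) × √(31/2).

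| Assumed s | Share of the 1.5-point target | Chance of p<0.05 |
|---|---|---|
| 0.25 | 17% | 7.6% |
| 0.5 | 33% | 15.7% |
| 0.75 | 50% | 29.4% |
| 1.0 | 67% | 47.1% |

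**The case against.** The strongest reply is that the tested treatment is MMRA as a whole. The Objective compares MMRA with sham, the MMRA section presents it as one clinic's protocol with stretching inside it, and the Background says that protocol was chosen to reflect practice. This stands, and it defeats the inference, which a reader might draw, that a positive result could not be credited to the treatment at all. It does not rescue the needling-only principle or the general statement in the Abstract.

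The stretching is also brief, and exercise advice is offered to participants without restriction to one arm. Both points make a large added effect less plausible. Neither removes the difference, because shared advice does not supply in-session stretching to the sham arm.

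Three stronger readings are tempting and are not supported:

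- **Meridian diagnosis as a second unmatched component.** The Intervention section describes palpation by meridian sinews and practitioner interaction for both groups. Individual against fixed points concerns where needles go, which can fairly be called needling.
- **Blinding shown to be weakened.** The Blinding section does not say the Park device is used at every point, and neither arm's first local step names it. Only the distal-point gap remains, in an article that leaves procedural detail to SOPs. Allocation guesses and credibility ratings are planned after the first and last treatments. They can detect unblinding, though not repair it.
- **An inflated false-positive rate.** For the package question, a real stretching effect is part of a true effect. The percentages above bear only on a claim about needling alone, under assumed effects.

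**Conclusion.** The contradiction holds for stretching. The control principle in the Intervention section and the procedures in the MMRA and Sham sections cannot both be right as written. This rests on reading the sham description as complete on this point, which is reasonable because it is set out step by step, down to distances, number of stimulations and retention time.

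A positive result would support the MMRA package, stretching included, over sham. It would not support an effect of needling alone or the Abstract's claim about acupuncture in general. The range-of-motion outcome needs the same caution, since its directions are the ones stretched.

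The size of any stretching contribution is unknown from the documents, and the sample size is unaffected. The Park device wording at distal points is a lesser item to clarify.

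**What to change.** Reconcile the Blinding, Intervention, MMRA and Sham sections so that the control principle and the described procedures agree, including whether the Park device is used at the MMRA distal points. Which procedure is right is for the investigators.

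If the stretching difference stands:

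- delete the claim that only the needling components differ;
- reword the Abstract's concluding statement to refer to the MMRA package, stretching included, versus sham;
- apply the same limit to the Background, where the sham device is said to allow evaluation of acupuncture's efficacy, and to the main Discussion, where physiological changes beyond placebo are attributed to acupuncture.

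On that route the change is to wording only, with no effect on the sample size or the analysis. The cost is a narrower conclusion.

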#### Myofascial-meridian release acupuncture (MMRA) treatment

The MMRA treatment is acupuncture protocol used at the Spine and Joint Clinical Center in Kyung Hee University Korean Medicine Hospital for patients with chronic neck pain. Chronic neck pain is related to local factors such as mechanical stress from the head or spine and systemic factors such as mental stress from psychosocial issues [16, 17]. Thus, the MMRA treatment was developed to reduce not only local factors by decreasing tissue adhesion [18] and myofascial trigger points [19, 20] but also systemic factors by promoting the flow of qi and blood [21] and reducing psychological factors [22].

A total of 8 acupuncture sessions will be performed using 0.25 × 40 mm disposable sterile acupuncture needles (Dongbang Acupuncture Inc., Chungnam, Republic of Korea). As for local points, a simple insertion technique is performed at EX-B2 and 5–10 tender points on the posterior neck followed by approximately 30 s of stretching, including flexion, extension, lateral bending and rotation. The acupuncture treatment is then performed at bilateral BL10, SI15, GB20, TE15 and CV14 using PSD and real needles. The needles are retained for 20 min, and the deqi sensation is induced by rotating the needles 3–5 times in a single direction (right and left if the patient expresses pain). A maximum of 4 individual acupuncture points are allowed. For distal points, a meridian diagnosis is carried out before the acupuncture treatment. If more than 2 meridians are diagnosed, a combination of acupuncture points from both meridians can be used.Greater yang meridian sinews (Smaller Intestine & Bladder meridian): BL65, SI3, Jeong-geun, Jeong-jongLesser yang meridian sinews (Triple Energizer & Gallbladder meridian): GB41, TE3, GB34, GB39Yang brightness meridian sinews (Large Intestine & Stomach meridian): LI11, Young-gol, Sang-bek, CV24.

After the meridian diagnosis is complete, 6 acupuncture points in the corresponding meridian group, as well as unilateral PC6 and HT7, will be chosen for the treatment. After penetration, the needles are retained for 20 min, and the deqi sensation is induced by rotating the needles 3–5 times in a single direction (right and left if the patient expresses pain). If CV24 is chosen, the needle should be rotated right and left for 30 s after penetration, during which time flexion stretching is performed, and then removed.

#### Sham acupuncture treatment

Park sham device (PSD) will be used as sham acupuncture. It is a validated sham acupuncture device that is comprised of two tubes and a needle (either real or sham) [23]. The guide tube supports the needle when penetrating the skin vertically. A larger tube named ‘Park tube’ is attached on the ring base and lets the guide tube move along the ‘Park tube’. A silicon base is attached to the skin by a double-sided tape [13]. A placebo acupuncture needle of PSD is indistinguishable with real acupuncture, but cannot penetrate the skin. For local points, predetermined points on the posterior neck (0.5 cm from C4, 5, 6, 7 on both sides) are stimulated lightly 2 times using sham acupuncture with a blunt tip of the needle. Then, a sham acupuncture treatment is performed using the PSD and sham acupuncture needles on the points 0.5 cm away from C5 and 6 on both sides and right above the spine of scapula. The needles are retained for 20 min. For distal points, 1 cm to the inner side of both TE6 and 0.3 cm to the outer side of the highest point of both calcaneus are treated using the PSD and sham acupuncture needles. The needles are retained for 20 min without a de-qi sensation, creating a false movement that is similar to twisting acupuncture.

#### Co-interventions

The participants in both groups will not be allowed to use a pain control intervention that is related to chronic neck pain and could influence study results, such as other acupuncture treatment, medication, physical therapy, manipulation therapy, transcutaneous electrical nerve stimulation, herbal medicine, injection therapy or operation. A maximum of 3 g per day of acetaminophen, the rescue medication to relieve neck pain, will be allowed, and a dose of rescue medication will be recorded in the case report form. Brochures about good posture and head & neck exercises that are effective for neck pain relief will be offered and taught to participants on the first visit.

### Outcome measurement

The detailed outcome measurement time points are provided in Table 1.

**Table 1 Tab1:** Schedule for the treatment and outcome measurements

Visit	S	1	2	3	4	5	6	7	8
Week		1		2			3	4	
Informed consent	●								
Demographic characteristics	●								
Vital signs	●	●	●	●	●	●	●	●	●
Blood test	●								●
Medical history	●								
Inclusion/Exclusion criteria	●								
Conformity assessment	●								
Treatment expectancy questionnaire	●								
Random allocation		●							
Treatment		●	●	●	●	●	●	●	●
Prescription of rescue medicine		●							
PI-NRS		●	●	●	●	●	●	●	●
NDI		●							●
CROM		●							●
HRV		●							●
Perceived stress scale		●							●
EQ-5D		●							●
PGIC									●
Pressure pain threshold		●							●
Consumption of rescue medicine									●
Days of restricted activity		●							●
Blinding test		●							●
Safety assessment		●	●	●	●	●	●	●	●

Visit 1: within 4 weeks after screening, Visit 8: 4 weeks after Visit 1 (+6 days)

*CROM* Cervical Range of Motion, *NDI* Neck Disability Index; *PGIC* Patient Global Impression of Change, *PI-NRS* 11-point Pain Intensity Numerical Rating Scale, *S* screening visit

#### Primary endpoint

The primary outcome is the mean change in the PI-NRS (0 = no pain and 10 = worst possible pain, 11-point Likert scale) from the baseline to 4 weeks. The PI-NRS has been widely used to assess chronic pain intensity in conditions such as chronic low back pain, fibromyalgia, osteoarthritis, diabetic neuropathy and post-herpetic neuralgia in placebo-controlled clinical trials [24]. In a previous study, the minimal clinically important change of PI-NRS score was 1.5 points in chronic neck pain patients [25]. Compared with global assessments of change in pain perception, the clinically important differences were a 30 % reduction of PI-NRS as “much improved” and a 50 % reduction of PI-NRS score as “very much improved,” regardless of disease, gender, age, study result or treatment group [24]. The participants will be instructed not to take a rescue medicine 4 h before assessing the pain intensity.

#### Secondary endpoint

The secondary outcomes include a change from the baseline of clinical relevance for pain (ratio of change greater than 1.5 in PI-NRS and decrease greater than 30 % and 50 % on the PI-NRS), function (NDI and Cervical Range of Motion (CROM)), autonomic and psychometric measurements (Heart Rate Variability (HRV) and Perceived Stress Scale (PSS)), quality of life (EuroQol (EQ-5D)), global assessment (Patient Global Impression of Change (PGIC)), semi-objective outcomes (pressure pain threshold (PPT), consumption of rescue medicine, days of restricted activity), immunologic and stress markers and adverse events.

##### Pain

The mean change of pain intensity from baseline at 1, 2, 3 weeks will be measured by the PI-NRS. Clinical relevance will be assessed using the ratio of participants in each group who reported PI-NRS scores that reduced greater than 1.5 points or 30 % and 50 % at 4 weeks from the baseline PI-NRS scores. We pre-defined the type of improvements as follows: a PI-NRS reduction of 1.5 points as minimally important; 30 % reduction from baseline as moderately important; and 50 % reduction as substantially important [26]. Therefore, in this trial, both the absolute and relative score change will be used to analyze the clinical relevance.

##### Disability

The function change in the neck will be evaluated using the Neck Disability Index (NDI) and cervical range of motion (CROM) from baseline to 4 weeks. The NDI is the most frequently used questionnaire to evaluate cervical pain and function limitation in daily life and consists of 10 questions ranging from 0 to 50 points. A higher score indicates more severe symptoms. The reliability and validity of the Korean version of the NDI was examined in 2009 by Song et al. [27]. The CROM of flexion, extension, lateral bending and rotation will be measured by a CROM device (Performance Attainment Associates, Lindstrom, MN, USA). A previous systematic review showed that the reliability and validity of the CROM device were favorable compared with other methods for assessing CROM [28].

